#### Sociodemographic and clinical history variables

2.9.3

Data on age, education, socioeconomic status, employment status, relationship status, ethnicity, nationality, number of children, number of people who comprised the family unit, pregnancy planning, pregnancy complications, baby's date of birth, mother and baby current health problems, prior and current psychological and psychiatric treatment (diagnosis, treatment type, and duration) and the presence of early experiences of sexual abuse and violence will be collected at the eligibility interview. Data on employment and relationship status will be updated at post-intervention and follow-up.

### Data collection and management

2.10

All data will be collected online via video call (interviews) or web platform (self-report questionnaires). Participants' data that can be directly traced to them (names, email addresses, and telephone numbers) will be coded to protect their privacy. Non-coded data will be saved separately, and only the principal researcher will have access to this data file. Self-report data will be collected using a secured online-based assessment system. All measurements collected during the study with their time points are shown in Table 2. An email account was created for the study to send participants allocation. Only the principal researcher will have access to the study email account. Semi-structured acceptability interviews will be recorded and transcribed. The transcriptions will have no personal data, and the recordings will be deleted after transcription.

**Table 2 t0010:** Overview of measures and assessment points.

Variable	Measure	Assessment points		
		T0	T1	T2
Sociodemographic and clinical history variables	Structured questions	x	Update on employment situation & relationship status	Update on employment situation & relationship status
Diagnostic interview	MINI	x	Only depression section	Only depression section
Intervention credibility and expectancy of benefit	CEQ-6	x		
Depression	PHQ-9	x	x	x
Postpartum depression	EPDS	x	x	x
Social support	MSPSS	x		x
Mother-infant bonding	PBS	x		x
Maternal satisfaction and self-efficacy	EEP	x		x
Engagement with the technology	TWEETS		x	
Satisfaction with the intervention	CSQ-8		x	

T0 = pre-treatment (baseline).

T1 = post-intervention (8 weeks after randomization).

T2 = follow-up (12 weeks after randomization).

MINI: Mini-International Neuropsychiatric Interview.

CEQ-6: Credibility and Expectancy Questionnaire-6.

PHQ-9: Patient Health Questionnaire-9.

EPDS: Edinburgh Postnatal Depression Scale.

MSPSS: Multidimensional Scale of Perceived Social Support.

PBS: Postnatal Bonding Scale.

EEP: Escala de Evaluación Parental.

TWEETS: TWente Engagement with Ehealth Technologies Scale.

CSQ-8: Client Satisfaction Questionnaire-8.

Regarding the data stored by the intervention, the web app uses secure HTTPS, which encrypts requests and responses. To register, participants must create a password that will be requested for signing in. A password also protects the admin/coach platform; only the principal researcher and the coaches have this password. The users' and the admin/coach platform's passwords are encrypted. The informed consent form includes information about the collection and management of personal data. More details about the management of the data stored by the app can be found in the Privacy Policy that participants must accept before registering, which they can return to later in the About section.

### Analyses

2.11

Statistical analysis of feasibility indicators is described in Table 1. The qualitative data from the interviews will be analyzed by two independent coders using thematic content analysis (Braun and Clarke, 2006). Themes will be identified, described, and subsequently categorized. Descriptive statistics will be reported, including the means and standard deviations (SDs) or medians and interquartile ranges for each questionnaire at T0, T1, and T2.

For preliminary efficacy on depressive symptomatology reduction, data will be analyzed following CONSORT guidelines; between-group comparisons will be by intention-to-treat. Missing data will be imputed using the Markov Chain Monte Carlo (MCMC) multivariate imputation algorithm. Comparison between groups will use repeated measures analysis of covariance (ANCOVA) with adjustment for baseline in a random-effects model. Interaction between time and group will be assessed (for changes in group effects with time). In the absence of such an interaction, the overall difference between groups across the two follow-up assessments will be calculated (95 % CIs and *p* values). Secondary analyses will include an adjustment for baseline characteristics. Other secondary outcomes will be analyzed with the same procedures.

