### Sample size

2.3

As feasibility studies are not expected to test statistical significance, the usual power calculation for clinical trials is not normally undertaken (Arain et al., 2010). However, some authors suggest using a sample size of 25 per group for pilot studies (Whitehead et al., 2016). Based on these recommendations and anticipating a possible dropout of 30 %, a sample size of 33 participants per group was set.

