### Randomization

2.6

Women who meet inclusion criteria will be randomized to “*Mamá, te entiendo*” or WL. An independent person not involved in the study will generate the allocation sequence. Stratified randomization will be conducted according to depressive symptom severity (minor or major depression). To generate the random allocation sequence, we will use the software Study Randomizer (2017) using permuted block randomization with block size of 6 in a 1:1 ratio. Researchers will be blind to the randomization process and will be notified through email regarding participant allocation by an independent researcher. Once randomized, participants and research personnel will not be blinded to group condition, except for T1 and T2 interviewers. Following the notification, participants will be contacted by email to inform them of their assigned group (i.e., intervention or WL). The intervention group will receive instructions for registering into the app.

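### The main between-group model omits the factor that randomisation is stratified by (minor or major depression), so its confidence intervals may be somewhat too wide

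*Protocol article*

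**What the plan says.** On allocation, section 2.6 (Randomization) states: "Stratified randomization will be conducted according to depressive symptom severity (minor or major depression". The sequence is generated "using permuted block randomization with block size of 6 in a 1:1 ratio".

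On analysis, section 2.11 introduces the comparison with "For preliminary efficacy on depressive symptomatology reduction, data will be analyzed following CONSORT guidelines" and then specifies the model: "Comparison between groups will use repeated measures analysis of covariance (ANCOVA) with adjustment for baseline in a random-effects model". Further covariates come in a separate sentence: "Secondary analyses will include an adjustment for baseline characteristics". These characteristics are not listed. The model is then extended to the remaining measures: "Other secondary outcomes will be analyzed with the same procedures". Section 2.9.2 gives these as social support, mother-infant bonding, maternal satisfaction and self-efficacy, and service use, alongside depression.

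**The concern.** Stratified blocks force near-balance between the arms on diagnosis, which removes one source of chance variation from the treatment estimate. A model that leaves the stratum out still counts the outcome difference between strata as residual noise, except for the part that the baseline score explains. The standard error it reports then exceeds the true sampling variation of the estimate.

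Section 2.11 promises 95% intervals and p values for these comparisons, and section 1.1 says that the trial is to supply parameters for a definitive trial. Intervals that are wider than the design warrants serve that purpose less well. The direction is conservative, so no false positive claim is at stake.

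**Working it through.** **Inputs from the protocol.** One stratification factor with two levels, blocks of 6, 1:1 allocation (2.6). Baseline is the only named covariate (2.11). The sample size starts from "some authors suggest using a sample size of 25 per group for pilot studies" and then allows for loss, "anticipating a possible dropout of 30" per cent: 25 × 1.30 = 32.5, rounded up to the stated 33 per group, so N = 66. With 30% lost, 33 × 0.70 = 23.1 per group remain, so N = 46 was checked as well. The protocol gives no standard error to reproduce.

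**Assumptions not in the protocol.** Within-stratum baseline-outcome correlation 0.5; share with major depression p = 0.5 or 0.7; baseline score d = 1.0 or 1.5 SD higher in the major stratum; effect of diagnosis on outcome at a given baseline score, g, from 0 to 0.8 SD. Standard errors are in within-stratum SD units. With complete data, the overall group effect from the repeated-measures model equals ANCOVA on the mean of T1 and T2, so that simpler form is used.

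**Closed form.**
- With the stratum, residual variance = 1 − 0.5² = 0.75.
- Without it, residual variance = 0.75 + g² × p(1−p) / [1 + d² p(1−p)].
- SE = √(residual variance × 4/N), with √(4/66) = 0.2462.

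For p = 0.5 and d = 1.0, the added term is g² × 0.25/1.25 = 0.20 g².

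| g (SD) | Residual variance, no stratum | SE, no stratum | SE, with stratum | Ratio |
|---|---|---|---|---|
| 0 | 0.750 | 0.213 | 0.213 | 1.00 |
| 0.3 | 0.768 | 0.216 | 0.213 | 1.01 |
| 0.5 | 0.800 | 0.220 | 0.213 | 1.03 |
| 0.8 | 0.878 | 0.231 | 0.213 | 1.08 |

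**Simulation.** 8,000 trials per scenario, stratified blocks of 6, no treatment effect. Results for N = 66 over all four combinations of p and d:

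| g (SD) | Reported SE, no stratum | Reported SE, with stratum | True SE, ratio without/with | Type I error, no stratum |
|---|---|---|---|---|
| 0 | 0.213–0.214 | 0.214 | 0.996–0.999 | 4.9–5.1% |
| 0.3 | 0.216 | 0.214 | 1.000–1.002 | 4.4–5.2% |
| 0.5 | 0.219–0.221 | 0.214 | 1.004–1.009 | 4.1–4.7% |
| 0.8 | 0.227–0.232 | 0.214 | 1.015–1.026 | 3.4–4.3% |

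With the stratum in the model, type I error is 4.6–5.3% throughout. N = 46 shows the same pattern: at g = 0.8 the reported SE is 5.5 to 8.2% larger without the stratum.

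The two tables separate two effects. At g = 0.8 the reported SE is 6 to 8% larger without the stratum, but the estimate itself varies only 1.5 to 2.6% more. Most of the gap is an overstated standard error, because the stratified allocation has already delivered the balance.

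**Outcomes whose baseline score tracks diagnosis less closely.** As an illustration, set d = 0, so that the baseline score carries no information on diagnosis. With p = 0.5 and g = 0.8, residual variance is 0.75 + 0.64 × 0.25 = 0.91, and the ratio is √(0.91/0.75) = 1.10.

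**The case against.** The strongest reply is that the cost may be nil. The PHQ-9 and EPDS measure the same symptoms that separate minor from major depression, so their baseline scores already carry much of what the stratum would add. If diagnosis adds nothing beyond them, the two models agree. This stands, and it is why the point is conditional.

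A second reply is that an article leaves the covariate list to a fuller plan, and that the unlisted baseline characteristics could include diagnosis. This stands only in part. The article is not silent: it names the adjustment in the main model and assigns other covariates to secondary analyses. Even if diagnosis is among those, the main comparison still omits it.

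Third, the primary outcomes are feasibility and acceptability, and no test was powered. This stands and sets the severity.

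Three stronger readings are tempting but not supported:
- **That precision is certainly lost.** At g = 0 nothing changes.
- **That intervals would be about 11% narrower with the stratum.** This needs g = 1.0: residual variance 0.95, SE 0.240 against 0.213. Diagnosis would have to shift the outcome by a full SD among women with the same baseline score, which nothing in the protocol supports. Even there, the true SE falls only from 0.219 to 0.212, about 3%.
- **That the MINI outcome loses its only baseline adjustment.** Its baseline value is the T0 diagnosis, which is the stratum. Baseline adjustment under the same procedures already includes it.

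**Conclusion.** The point holds as a minor one. As written, the main model leaves out the factor used to stratify randomisation. If diagnosis predicts outcome beyond the baseline score, the reported standard errors and 95% intervals will be somewhat too wide and the tests conservative, with no bias in the estimate.

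The range of 0 to about 8% in the reported standard error, and 0 to about 3% in true precision, rests on the assumed 0 to 0.8 SD effect of diagnosis and on the other assumed values above. It could be larger for bonding, social support and maternal self-efficacy, but the protocol gives no figures to settle that. No claim is made for the MINI outcome. Only secondary, preliminary-efficacy results are affected.

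**What to change.** In section 2.11, state that the main model for the PHQ-9, EPDS and other questionnaire outcomes includes the randomisation stratum (minor or major depression at T0) as a fixed covariate, alongside arm, time, their interaction and the baseline score. Keep the other baseline characteristics for the secondary analyses. The MINI outcome needs no change on this account.

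The cost is one phrase and one degree of freedom. No new data are needed, since the T0 diagnosis is recorded for every woman before randomisation. If the stratum proves uninformative, the loss is negligible: the simulated reported SE is 0.213–0.214 without it and 0.214 with it.

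### The pooled T1/T2 depression effect is reported only if a weak time-by-group test finds nothing, so which effect is estimated depends on the data; three secondary outcomes cannot follow the rule at all

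*Protocol article*

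**What the plan says.** Section 2.11 (Analyses) plans a baseline-adjusted repeated-measures ANCOVA with random effects for preliminary efficacy on depressive symptoms. It then gives a two-step rule. First, "Interaction between time and group will be assessed". Second, "In the absence of such an interaction, the overall difference between groups across the two follow-up assessments will be calculated", with 95% CIs and p values. The remaining secondary outcomes are to be handled by the same procedures.

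Section 2.1 places T1 at 8 weeks (end of treatment) and T2 at 12 weeks. Section 2.3 (Sample size) gives no power calculation: "As feasibility studies are not expected to test statistical significance, the usual power calculation for clinical trials is not normally undertaken". The size rests on a rule of thumb ("some authors suggest using a sample size of 25 per group for pilot studies") plus an allowance for 30% dropout, and "a sample size of 33 participants per group was set". Section 2.6 allocates 1:1.

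Table 2 lists the PHQ-9 and EPDS at T0, T1 and T2. It lists the MSPSS, the bonding measure and the EEP at T0 and T2 only.

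**The concern.** A non-significant interaction is treated as permission to average the two visits. In a trial of this size, that result may only mean the test could not see a change. Whether the report gives a two-visit average or something else is then settled by a noisy test rather than in advance.

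A changing effect is plausible here: T1 closes an 8-week guided programme and T2 falls four weeks later. If the effect fades or grows, the average describes neither visit. Someone planning the definitive trial needs to know whether the between-group figure is an end-of-treatment effect, a follow-up effect or a mixture.

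There is also a plain mismatch within the article: a rule that needs two follow-up assessments is extended to outcomes that have only one.

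**Working it through.** **Inputs from the protocol.** 33 per arm, 1:1 (sections 2.3 and 2.6). Dropout 30% (section 2.3), so 33 × 0.70 = 23.1, about 23 completers per arm. Two follow-up visits (section 2.1). The plan states no power for the interaction test, so there is no figure of its own to reproduce.

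**Assumptions, not in the protocol.** Two-sided 5% as the criterion for an interaction (suggested only by the 95% CIs). Residual correlation between T1 and T2, rho, from 0.5 to 0.8. Equal variance at both visits, effects in residual SD units. The arm sizes 23 and 33 bracket the information left after imputation.

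**Step 1: precision of the interaction contrast.** SE = sqrt[(2/n) × 2(1 − rho)].
- n = 23: sqrt[(2/23) × 2 × 0.5] = 0.295 at rho 0.5; sqrt[(2/23) × 2 × 0.2] = 0.187 at rho 0.8.
- n = 33: 0.246 at rho 0.5; 0.156 at rho 0.8.

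**Step 2: power, from the non-central t with 2n − 2 degrees of freedom.**

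| Change in effect, T1 to T2 | n per arm | rho 0.5 | rho 0.6 | rho 0.7 | rho 0.8 |
|---|---|---|---|---|---|
| 0.3 SD | 23 | 17% | 20% | 25% | 35% |
| 0.3 SD | 33 | 22% | 27% | 34% | 48% |
| 0.6 SD | 23 | 51% | 61% | 73% | 88% |
| 0.6 SD | 33 | 67% | 77% | 87% | 97% |

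The test is weak for a modest change and reasonably informative for a large one.

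**Step 3: what the rule then reports.** Take an illustrative true effect of 0.6 SD at T1 and 0.3 SD at T2. The pooled value is (0.6 + 0.3)/2 = 0.45 SD. With equal variances the average and the difference of the two visits are uncorrelated, so conditioning on a non-significant difference leaves the expected average at about 0.45. The rule reports it with probability 1 − power, from 1 − 0.48 = 52% (n = 33, rho 0.8) to 1 − 0.17 = 83% (n = 23, rho 0.5). That figure is 0.15/0.6 = 25% below the T1 effect and 0.15/0.3 = 50% above the T2 effect.

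A separate simulation started from 0.64 SD, the meta-analytic effect cited in section 1, and halved it to 0.32 SD by T2 (rho 0.5 or 0.7, baseline correlation 0.5). The pooled value, about 0.48 SD, was reported in 62% to 75% of trials with 33 per arm and 74% to 82% with 23 per arm.

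**Step 4: the rule against Table 2.** A time-by-group interaction after baseline adjustment needs at least two follow-up visits. The MSPSS, bonding measure and EEP have one (T2). Neither the interaction nor the two-visit difference exists for them.

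**The case against.** Several points on the other side stand.

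- The analysis is labelled preliminary efficacy and depression is a secondary outcome. The definitive trial is made to depend on feasibility and acceptability, so nothing in the feasibility conclusions changes.
- Means and SDs (or medians and interquartile ranges) are promised for every questionnaire at each visit. An unadjusted T1 contrast can therefore be recovered even when the pooled figure is the one reported.
- The 0.15 SD shift in the example is well inside the uncertainty at one visit: the 95% CI half-width is about 0.42 SD (n = 33) to 0.50 SD (n = 23), assuming a baseline correlation of 0.5.
- The article does not name the estimate to be given when an interaction is found. Visit-specific differences are the natural reading, and a condensed article may leave that to the analysis plan. It is not held against the plan here.

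Three stronger readings are tempting but not supported.

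- A reader might infer that p values contradict section 2.3. That sentence ("As feasibility studies are not expected to test statistical significance") is a general reason for omitting a power calculation; it does not rule out p values. There is some tension of purpose, not a contradiction.
- A reader might count about seven tested outcomes and quote 1 − 0.95^7 = 30% for at least one false positive. That requires seven independent tests. The outcomes are related measures in the same women, and the pooled estimate applies only to the PHQ-9 and EPDS. In simulation with no true effect, the pre-test raised false positives on one scale only to about 6% to 7%.
- A reader might infer that the pooled figure will size the next trial. Section 1.1 says the feasibility outcomes supply the design parameters, so that use is possible but not stated.

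What remains is the conditional rule itself, which the article fixes and which is not a missing detail.

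**Conclusion.** The point holds for the PHQ-9 and EPDS. At the planned size, finding no interaction will often reflect low power rather than a constant effect, so the quantity estimated becomes data-dependent and a modest fade or growth would usually be averaged away. The ranges in the working rest on the assumed 5% criterion and correlations of 0.5 to 0.8; the 0.6-to-0.3 SD pattern is an illustration, not a prediction. The claim of low power should not be carried over to large changes combined with high correlation.

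The mismatch for the MSPSS, bonding and EEP needs no assumption: the procedure described cannot be run on the data Table 2 collects.

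This should be corrected, but it is confined to the secondary efficacy analysis.

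**What to change.** Rewrite the end of section 2.11 along these lines:

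- Keep the group-by-time term in the PHQ-9 and EPDS models. Always report the baseline-adjusted group differences at T1 (named in advance as the main estimate) and at T2, each with a 95% CI, whatever the interaction test shows. The T1-T2 average may be added.
- For the MSPSS, bonding measure and EEP, report the baseline-adjusted difference at T2 with a 95% CI.
- Label any p values as exploratory, in keeping with section 2.3.

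The cost is a few sentences and no new data. Visit-specific intervals are somewhat wider than the pooled one: the pooled SE is sqrt[(1 + rho)/2] of the single-visit SE, which is 0.87 at rho 0.5 and 0.95 at rho 0.8. Each single-visit interval is therefore about 15% (1/0.866 = 1.15) to 5% (1/0.949 = 1.05) wider.

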## Discussion

3

“*Mamá, te entiendo*” was developed in response to the high rates of PPD, the barriers to mental health care from both women and health care providers, and the increased use of smartphones and perinatal apps in Chile. Evidence shows that PPD is associated with overall poor maternal (O'Hara and McCabe, 2013; Gjerdingen and Yawn, 2007; Slomian et al., 2019) and infant health (Stein et al., 2014; Slomian et al., 2019; Hayes et al., 2013; Pawlby et al., 2009), even when the symptomatology is subclinical (Tronick and Reck, 2009; Weinberg et al., 2001). Internet-based interventions could alleviate some pressure put on in-person health care services and overcome barriers to help-seeking, providing an alternative or complementary option for widespread perinatal mental health care provision (Spadaro et al., 2022).

The study presented in this protocol will examine the feasibility and acceptability of “*Mamá, te entiendo*” (“Mom, I get you”), a guided cognitive behavioral app-based intervention for reducing postpartum depression symptomatology and preventing the onset of major depression. Assessing the feasibility and acceptability of complex interventions and study procedures are strongly recommended to estimate important parameters and answer key uncertainties required to inform the design of future trials (Eldridge et al., 2016). Given the novelty of the intervention in the country, assessing the acceptability and feasibility of the intervention and study procedures is of great importance in informing intervention refinements and planning a future definitive controlled trial.

One strength of this study is the approach used to develop the intervention, which tries to fulfill the needs of Chilean perinatal women. The development process of the intervention was based on the “CeHRes Roadmap” (van Gemert-Pijnen et al., 2011), which includes the involvement of potential end users and other stakeholders. Also, collecting both quantitative and qualitative data for answering the research questions provides more in-depth findings and can balance out the limitations of each method. On the other hand, some challenges could be expected in this study. Postpartum women will be self-referred to this trial. It is possible that only highly motivated women will be included in our study; thus, the sample will not represent all Chilean women with postpartum depression symptoms.

Regarding the guidance delivered by the e-coach, challenges may arise related to the amount of support provided versus the amount of support expected or needed by the mothers. On the other hand, to assess who would benefit most from the intervention, including more instruments that assess participants' characteristics (like resilience, personality traits, or birth trauma) would have been optimal. However, we tried to keep the number of instruments short not to compromise participants' adherence.

If the intervention and procedures prove feasible and acceptable, the next step will be to study the intervention in a definitive controlled trial. If the intervention demonstrates to be effective, the aim is to implement it within the Chilean healthcare setting.

